### Outcomes

#### Primary Outcome

The primary outcome of preliminary efficacy is the difference in the proportion of sexually active adolescents and young adults tested for Neisseria gonorrhoeae or chlamydia trachomatis between the 2 arms based on the EMR review. We selected preliminary efficacy as the primary outcome because the trial was designed and powered to provide an effect size estimate that would inform the design and sample size calculations for a future multisite trial. While many pilot studies emphasize feasibility and acceptability as primary outcomes, in this single-site trial, we aimed to generate robust preliminary data on testing uptake to guide scale-up and ensure generalizability across diverse ED settings.

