### Statistical Analysis

We will summarize efficacy and implementation outcomes using standard descriptive statistics for continuous and categorical variables. We will conduct bivariate analyses to identify balance in the random allocation of the intervention across providers and patient characteristics.

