#### Preliminary Efficacy

An intent-to-treat analysis of all enrolled patients will be conducted according to random assignment of the intervention to estimate the effect of STIckER on STI testing. We will conduct a mixed-effects generalized linear model (GLM) with the logit link function to look at the effect of STIckER on STI testing, if there is a clustering effect by provider, or logistic regression if there is no provider effect. To determine whether there is a provider effect, we will assess the intraclass correlation coefficient (ICC) for the primary outcome using a null (empty) mixed-effects model with provider as a random effect. If the ICC is greater than 0.01, we will proceed with mixed-effects modeling; otherwise, we will use standard logistic regression. For other dichotomous outcomes, we will use the same analytic approach (GLM) with the logit link function if there is a provider effect or logistic regression if there is no provider effect.

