### Power Analysis

This pilot trial will enroll 44 providers and 140 adolescent and young adult patients over 6 months based on feasibility. Using a simple, parallel randomized design and accounting for providers evaluating more than 1 patient, we estimate the minimum detectable effect size (MDE) of 0.348. MDE is based on the following assumptions: α=.05, a 2-tailed test, with 80% power, and ICC of 0.01, 50% of variance in adolescents and young adults, and 50% of variance in providers explained, and all other covariates of interest (eg, age and gender) were balanced by randomization of STIckER to providers and their adolescent and young adult patients. With our sample size of 140 participants, we have the power to detect a minimum of 35% higher likelihood of being tested for STIs in the intervention arm compared to usual care.

The ICC of 0.01 and the assumption that 50% of the variance would be attributable to provider- versus patient-level factors were based on conservative estimates. These assumptions are intended to ensure sufficient power while accounting for possible provider clustering.

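### The primary outcome is a difference in proportions, the planned models give odds ratios, and the detectable effect is a standardised figure misread as a 35% gain

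*Protocol article*

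**What the plan says.** All references are to the protocol article.

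- **Primary Outcome** fixes the measure: "The primary outcome of preliminary efficacy is the difference in the proportion of sexually active adolescents and young adults tested". This is a risk difference between arms, taken from the medical record. The section also gives the purpose: "the trial was designed and powered to provide an effect size estimate that would inform the design and sample size calculations for a future multisite" (a later study). It does not name the scale of that effect size.
- **Statistical Analysis** (opening paragraph): "We will summarize efficacy and implementation outcomes using standard descriptive statistics for continuous and categorical variables".
- **Preliminary Efficacy** names the models for the primary outcome. Where clustering by provider is found, the plan is: "We will conduct a mixed-effects generalized linear model (GLM) with the logit link function to look at the effect of STIckER on STI testing". The alternative, where clustering is absent, reads: "or logistic regression if there is no provider effect". The choice follows a cut-off: "If the ICC is greater than 0.01, we will proceed with mixed-effects modeling; otherwise, we will use standard logistic regression".
- **Power Analysis** gives a minimum detectable effect of 0.348 for 44 providers and 140 patients (two-sided 5% level, 80% power, ICC 0.01, half the variance explained at each level). For the intervention arm, it translates this as: "35% higher likelihood of being tested for STIs". It does not say whether the 35% is relative or absolute, and it gives no control testing rate.

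**The concern.** One outcome is described on three scales, and nothing in the text links them: a risk difference in the definition, an odds ratio from either model, and a standardised effect in the power statement.

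The first mismatch matters because an odds ratio alone does not determine a risk difference. The crude difference from the descriptive summaries is on the right scale, but no interval allowing for provider randomisation is planned for it. The stated purpose is an estimate for planning a multisite trial, and such planning needs both the estimate and its uncertainty.

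The second mismatch matters because a reader of the Power Analysis cannot tell what effect the trial could detect. A standardised effect of 0.348 is not a 35% increase in anything unless the control rate happens to make it so.

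**Working it through.** **1. Reproducing 0.348.** Inputs from the Power Analysis: J = 44 providers, N = 140 patients, ICC = 0.01, R² = 0.50 at both levels, two-sided α = 0.05, 80% power. The standard two-level formula for a standardised effect with 1:1 allocation and J − 2 = 42 degrees of freedom is

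MDE = (t₀.₉₇₅ + t₀.₈₀) × √{4[ICC(1 − R²)/J + (1 − ICC)(1 − R²)/N]}

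- Multiplier: 2.0181 + 0.8503 = 2.8683
- Variance: 4 × (0.000114 + 0.003536) = 0.014597; square root 0.12082
- MDE = 2.8683 × 0.12082 = **0.3466** (0.3478 with the 139 patients enrolled), against 0.348 stated

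The published figure is therefore in standard-deviation units. It is neither a risk difference nor an odds ratio.

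**2. Converting 0.348 to percentage points.** The control rate p₀ is an assumption. Solve (p₁ − p₀)/√{p̄(1 − p̄)} = 0.348, with p̄ the mean of the two rates:

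| Assumed p₀ | p₁ | Difference | Risk ratio |
|---|---|---|---|
| 10% | 22.9% | 12.9 points | 2.29 |
| 20% | 35.6% | 15.6 points | 1.78 |
| 30% | 46.9% | 16.9 points | 1.56 |
| 40% | 57.4% | 17.4 points | 1.43 |
| 50% | 67.1% | 17.1 points | 1.34 |

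The arcsine conversion gives nearly the same range (12.6 to 17.3 points). Using the control-arm standard deviation alone gives 10.4 to 17.4 points. Treating 0.348 as an effect on the latent logit scale (odds ratio about 1.88) gives 7.3 to 15.6 points. None approaches 35 points, and the implied risk ratio is near 1.35 only if about half of control patients are tested.

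**3. Power under the two readings of 35%.** Two-proportion test, 70 per arm, design effect 1 + (140/44 − 1) × 0.01 = 1.022, so 68.5 effective patients per arm; no covariate adjustment:

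| Assumed p₀ | Power at +35 points | Power at risk ratio 1.35 |
|---|---|---|
| 10% | 99.8% | 9% |
| 20% | 99.3% | 16% |
| 30% | 98.9% | 25% |
| 40% | 99.0% | 37% |
| 50% | 99.5% | 55% |

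On this unadjusted basis, 80% power needs a difference of about 19 to 24 points. That is more than the 13 to 17 above because the published figure assumes half the variance is explained.

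**4. What an odds ratio says about the defined outcome.** With odds ratio 2.0, p₁ = 2p₀/(1 + p₀). The difference is 8.2, 13.3, 16.2 and 16.7 points at control rates of 10%, 20%, 30% and 50%. The model's output alone does not fix the defined quantity.

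**5. What a crude interval leaves out.** With 3.18 patients per provider (equal numbers assumed), ignoring clustering makes the interval too narrow by a factor √{1 + 2.18 × ICC}: 1.01 at ICC 0.01, 1.10 at 0.10 and 1.20 at 0.20.

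**6. The switch between models.** The mixed model's odds ratio is conditional on provider; that from plain logistic regression without covariates is marginal. Integrating over a normal provider effect with logit-scale variance ICC/(1 − ICC) × π²/3, at control rates of 20% to 50%, a conditional odds ratio of 2.0 corresponds to a marginal one of about 1.99 at ICC 0.01, 1.95 to 1.96 at 0.05, 1.90 to 1.91 at 0.10 and 1.81 to 1.83 at 0.20. At ICC 0.20 and a 30% control rate the difference is 13.7 points, against 16.2 if the odds ratio were read as marginal.

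**The case against.** The strongest reply is that defining an outcome as proportions and testing it with a logit model is ordinary practice. The descriptive summaries will show the proportion tested in each arm, hence the crude difference. A control proportion plus an odds ratio can feed a sample-size calculation. A risk difference can be standardised from either planned model, and an article may leave that step to a fuller plan that is not shown. All of this stands. A reader might infer that the trial will yield no usable effect size; the documents do not support that.

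A reader might also infer that the ICC rule makes the result uninterpretable, because it changes what the odds ratio means. The arithmetic does not bear this out: at the 0.01 threshold the two odds ratios differ by under 1%, and the gap is about 9% at ICC 0.20. It is a minor point.

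Nor does the text present an odds ratio as a relative gain in likelihood. The 35% glosses the standardised 0.348, so figures for how far an odds ratio exaggerates a risk ratio would measure an error the article does not make.

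Two things remain. The article itself states the outcome measure and the models, and they are on different scales. The misreading of 0.348 is in the article's own words, so an unseen plan cannot account for it.

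**Conclusion.** The point holds in two parts.

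First, no planned model gives the defined difference in proportions with an interval that accounts for provider randomisation. The loss is modest if the ICC is near 0.01 and grows with it, to an interval about 20% too narrow at 0.20 if the crude difference is used without allowance for clustering.

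Second, the power sentence is wrong as worded. The 0.348 is a standardised effect of about 13 to 17 percentage points at assumed control rates of 10% to 50%, less at low control rates under some conversions. It does not generally mean a 35% gain: a risk ratio of 1.35 has 9% to 55% unadjusted power over that range.

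These sizes rest on assumed control rates, since none is stated, and on the article's own ICC and variance-explained values where 0.348 is taken as given. Enrolment is complete and the Results section says primary analyses are under way, so the headline measure should be settled before results are reported.

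**What to change.** - State the marginal risk difference with a 95% confidence interval as the estimate of the primary outcome. Obtain it by standardising predicted probabilities over all enrolled patients from one clustered model, used whatever the estimated ICC, with a provider-level bootstrap or a small-sample-corrected interval.
- Report the odds ratio alongside it, and say whether it is conditional on provider or marginal.
- Restate the detectable effect in percentage points at a stated, assumed control testing rate, name 0.348 as a standardised effect, and drop the 35% wording.

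No new data are needed. The cost is a little more analysis work and a power statement that reads differently from the published one.

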#### Secondary Outcomes

Secondary efficacy outcomes include rates of extragenital Neisseria gonorrhoeae or chlamydia trachomatis testing, overall and site-specific STI positivity rate, decisional conflict, and level of shared decision-making. Secondary implementation outcomes include feasibility (FIM), acceptability (AIM), appropriateness (IAM), and personal traits and attitudes toward STI screening.

### Statistical Analysis

We will summarize efficacy and implementation outcomes using standard descriptive statistics for continuous and categorical variables. We will conduct bivariate analyses to identify balance in the random allocation of the intervention across providers and patient characteristics.

#### Preliminary Efficacy

An intent-to-treat analysis of all enrolled patients will be conducted according to random assignment of the intervention to estimate the effect of STIckER on STI testing. We will conduct a mixed-effects generalized linear model (GLM) with the logit link function to look at the effect of STIckER on STI testing, if there is a clustering effect by provider, or logistic regression if there is no provider effect. To determine whether there is a provider effect, we will assess the intraclass correlation coefficient (ICC) for the primary outcome using a null (empty) mixed-effects model with provider as a random effect. If the ICC is greater than 0.01, we will proceed with mixed-effects modeling; otherwise, we will use standard logistic regression. For other dichotomous outcomes, we will use the same analytic approach (GLM) with the logit link function if there is a provider effect or logistic regression if there is no provider effect.

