#### Randomization and Allocation

To avoid contamination, 50 HCPs were randomized 1:1 to the intervention (STIckER) or control arm. The allocation sequence was computer-generated by the study epidemiologist using a simple randomization method with stratification by location (adult vs pediatric ED). The randomization sequence was implemented by a study coordinator using a centralized allocation system. The assignment was not concealed from investigators. Randomization health care provider participant (HCP-P) in the intervention arm received 1:1 training with a research assistant on the STIckER app. If a participating provider left the ED before the end of the study period, a new provider randomized to the same study arm was invited to participate.

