### Intervention

Adolescents and young adults between the ages of 15 and 24 years attending the ED during the time that an HCP trained on STIckER was on service would scan the STIckER app before seeing the provider. patients as study participants (HCP-Ps and adolescent and young adult participants).

Adolescent and young adult participants are assigned to the arm of the provider to whom they are assigned. Adolescent and young adult participants with intervention-arm providers will scan a QR code with their personal mobile device, linking them to the web-based STIckER app. They will interact with the app, completing a sexual health assessment and indicating their personal values and preferences before being led to a final infographic to be shown to the HCP-P. This infographic will alert the provider to both the adolescent and young adult participants’ need for oral, rectal, or urinary STI testing and their preference for testing.

Adolescent and young adult participants with control-arm providers will also scan a QR code with their personal mobile device, but it will lead them to a landing page with a prompt informing them they can ask their provider about STI testing. They will not have access to the digital tools and shared decision-making modules within the STIckER app.

All adolescent and young adult participants are followed throughout the ED visit. Adolescent and young adult participants will complete questionnaires at enrollment and upon ED discharge. These questionnaires comprise a comprehensive set of predominantly validated instruments and will capture sociodemographic characteristics, sexual behavior, substance use, perceived HIV risk, patient satisfaction, and decision-making quality. HCP-P will also complete a questionnaire after each adolescent and young adult visit and an end-of-study questionnaire focused on STIckeR implementation.

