### Study Assessments

#### HCP-P Study Assessments

At enrollment, enrolled HCP-Ps will complete a basic demographic questionnaire. (age, race, ethnicity, sex at birth, gender identity, years since completing training, and type of clinical training completed).

The exit survey will be conducted immediately after a visit with an adolescent and young adult participant; the HCP-P will complete an exit survey.

HCP-Ps randomized to the control arm get questions on whether STI testing was discussed (“Did you and your patient discuss STI testing”), if the discussion was appropriate (Likert scale of 1‐5, from “completely appropriate” to “completely inappropriate”), if STI testing was ordered, and if STI testing was ordered what level of shared decision-making involvement occurred using the Control Preferences Scale (Likert scale of 1 to 5, from “I made the decision on my own” to “the patient made the decision on their own”) [22].

HCP-Ps randomized to the intervention will get the same questions on whether STI testing was discussed, if the discussion was appropriate, if STI testing was ordered, and if STI testing was ordered, what level of shared decision-making involvement occurred using the control preferences scale. They will also complete validated questions on implementation (acceptability of intervention measure [AIM], intervention appropriate measure [IAM], and feasibility of intervention measure [FIM]) [23].

The postsurvey will be conducted after completing their participation in the STIckER study (a maximum of 6 adolescent and young adult participants or the study completing overall enrollment), HCP-P will complete a postintervention questionnaire.

HCP-Ps, randomized to the control arm, will complete a self-efficacy questionnaire to measure their clinical communication skills [24].

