#### Secondary Efficacy and Implementation Outcomes

If there is a provider-level effect, we will use mixed-effect GLM to look at the association of STIckER on the continuous outcomes, such as implementation scales, and linear or logistic regression if there is no provider effect. If needed, we will also conduct sensitivity analyses to explore the effect of spillover, misclassification, missing data, or any other deviation from the study procedures that would affect efficacy or implementation outcomes.

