## Results

Enrollment began in September 2023 and was completed in July 2025, with 44 providers and 139 adolescent and young adult participants enrolled across adult and pediatric EDs. All participants’ follow-up and survey data collection are complete. Data cleaning and primary analyses are currently underway, with dissemination of final results anticipated in late 2025.

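### Provider, the unit of randomization, can be dropped from the analysis by a 0.01 ICC cut-off that 44 providers with about three patients each cannot resolve; the exposure is in the two-arm secondary outcomes

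*Protocol article*

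**What the plan says.** Randomization and Allocation in the Protocol article makes the provider the randomized unit: "50 HCPs were randomized 1:1 to the intervention (STIckER) or control arm". Patients inherit the arm, as the Intervention section states: "Adolescent and young adult participants are assigned to the arm of the provider to whom they are assigned".

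For the primary outcome, tested or not tested for gonorrhea or chlamydia, Preliminary Efficacy sets a preliminary check: "we will assess the intraclass correlation coefficient (ICC) for the primary outcome using a null (empty) mixed-effects model with provider as a random effect". The decision rule follows: "If the ICC is greater than 0.01, we will proceed with mixed-effects modeling; otherwise, we will use standard logistic regression". Other dichotomous outcomes are then handled in the same way, depending on whether a provider effect exists. Secondary Efficacy and Implementation Outcomes repeats the switch for continuous outcomes, with "linear or logistic regression if there is no provider effect". The Abstract also makes mixed models conditional on clustering being found. The only definition of a provider effect anywhere in the article is the primary outcome's ICC.

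The Power Analysis section assumes an ICC of 0.01, the same value as the cut-off.

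**The concern.** When providers are randomized, patients of one provider share both the arm and that provider's habits. An analysis that treats them as independent understates the standard error whenever the outcome is correlated within provider. The plan makes this protection depend on a preliminary estimate, which raises three questions:

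- Can a sample of this size tell an ICC above 0.01 from one below it?
- Does an empty model give the right ICC, when arm varies only between providers?
- Should the ICC of one outcome decide the model for outcomes that may cluster differently?

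The rule is written out in the article, so it is not a detail left to an unseen analysis plan. At stake are the error rate and interval width of the secondary comparisons, and the ICC that this pilot hands to the multisite trial.

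**Working it through.** **Inputs from the article.** Power Analysis: "This pilot trial will enroll 44 providers and 140 adolescent and young adult patients over 6 months based on feasibility". Results: "with 44 providers and 139 adolescent and young adult participants enrolled across adult and pediatric EDs". Mean patients per provider m = 140/44 = 3.18. HCP-P Study Assessments ends a provider's participation at "a maximum of 6 adolescent and young adult participants or the study completing overall enrollment". Power Analysis also gives two-sided alpha 0.05, 80% power, ICC 0.01 and 50% of variance explained at each level.

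**Assumed, not in the article.** Control testing rate 30% or 50%; cluster sizes near-equal (36 providers with 3 patients, 8 with 4) or spread from 1 to 6; ICC on the latent logistic scale; secondary-outcome ICC of 0.10 or 0.20; primary and secondary outcomes independent of each other.

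**1. The plan's own figure.** MDE = M × sqrt{ρ(1−R²)/(0.25 × 44) + (1−ρ)(1−R²)/(0.25 × 140)}, where M is the sum of the 97.5% and 80% t quantiles on 42 df. The terms are 0.01 × 0.5/11 = 0.00045 and 0.99 × 0.5/35 = 0.01414, and the square root of their sum is 0.1208. The result is 0.347 with 140 patients and 0.348 with 139. The stated 0.348 is reproduced, so the design calculation does carry a provider term.

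**2. Precision of the ICC.** SE = sqrt{2(1−r)²[1+(m−1)r]²/[m(m−1)(k−1)]}. With k = 44, m = 3.18 and r = 0.01, this is sqrt(2.047/298.5) = 0.083, about eight times the cut-off.

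**3. How the rule behaves.** Random-intercept logistic models were fitted by maximum likelihood, 1,500 simulated trials per setting, with no treatment effect.

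| True ICC | Clustering dropped |
|---|---|
| 0 | 58-60% |
| 0.01 | 54-58% |
| 0.05 | 39-44% |
| 0.10 | 24-29% |
| 0.20 | 6-10% |

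Two further sets of runs gave 57%, 40% and 26%, and 56%, 41% and 21%, at ICC 0.01, 0.05 and 0.10. At a true ICC of 0.01, just over half of the fits estimate the ICC as exactly zero. The rule scarcely separates no clustering from the planning value.

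**4. Arm left out of the empty model.** With half the providers in each arm, an odds ratio of 2 and no other provider variance, the between-provider variance on the logit scale is (ln 2/2)² = 0.120. The implied latent ICC is 0.120/(0.120 + π²/3) = 0.035. In simulation with zero within-arm clustering, an odds ratio of 4 raised the chance of keeping the mixed model from 0.40-0.42 to 0.83-0.87, and the median estimated ICC from 0 to 0.12-0.14.

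**5. Primary outcome.** Under no treatment effect, the rejection rate of the two-step rule equals that of always using the mixed model to three decimals in every setting (0.053 for both at ICC 0.10 and a 30% rate, for example).

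**6. Secondary outcome switched by the primary ICC.** Primary ICC 0.01, sizes 1 to 6, binary secondary outcome, 1,200 trials. Clustering was dropped in 698 of them (58%).

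| Secondary ICC | Always mixed | Rule, overall | Rule, when dropped |
|---|---|---|---|
| 0.10 | 0.054 | 0.068 | 0.080 |
| 0.20 | 0.062 | 0.086 | 0.110 |

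Monte Carlo standard error is about 0.007 for the overall columns and 0.011 for the last. As a rough check that also covers continuous scales, the design effect is 1 + 2.18 × ICC, or 1.22 and 1.44. Ignoring it gives 2[1 − Φ(1.96/√DE)] = 0.076 and 0.102, in line with the last column.

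**The case against.** The strongest reply is that the rule does little harm where it matters most, and that stands. When the empty-model ICC is 0.01 or less, the mixed model with arm nearly collapses to ordinary logistic regression. Drop rates also fall as clustering grows, and the near-even split occurs where the design effect is only about 1.02 (ICC 0.01) to 1.11 (ICC 0.05). Omitting arm pushes toward keeping the mixed model, so that flaw is conservative for false positives.

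Three stronger readings are tempting and should not be drawn:

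- **That the primary effect estimate is biased when clustering is dropped.** With odds ratio 2 and a 35% control rate, the log odds ratio in gated-out trials is low by 0.109 at ICC 0. The mixed model with arm, fitted to the same trials, is low by the same 0.109; over all trials its bias is about 0.01. Selecting trials by the gate produces the shift, not the choice of logistic regression.
- **That the estimand changes materially.** At the cut-off, provider-specific and population-average log odds ratios differ by about 0.6%.
- **That false-positive rates run far above 10% on provider-rated scales.** This needs ICCs for which the article gives no basis. The acceptability, appropriateness and feasibility measures are collected only in the intervention arm (HCP-P Study Assessments; Exit Survey), so they have no arm contrast. Provider self-efficacy is completed once per provider. The Control Preferences Scale is asked only when testing was ordered, which leaves fewer records per provider.

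It can also be said that the article may intend a fresh ICC check for each outcome. The wording allows this. The same unreliable gate would then recur for each outcome, and the text would still need to say so.

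**Conclusion.** The point holds as a should-fix. The article lets a provider-randomized trial drop provider on an estimate whose standard error is about eight times the cut-off. Primary-outcome inference is essentially unaffected. The exposure lies in patient-level secondary outcomes measured in both arms, such as decisional conflict and the shared decision-making rating, if the primary outcome's ICC decides their model, as the text literally reads. The inflation is modest: about 7-9% overall and 8-11% when clustering is dropped, against 5-6% if it is always kept. These figures rest on assumed secondary ICCs of 0.10 to 0.20, independence from the primary outcome, and a binary outcome recorded for every patient; fewer records per provider would make the inflation smaller.

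Separately, an ICC from a model without arm mixes treatment effect with provider variation. That makes it a poor planning value, although the Primary Outcome section gives informing the next trial's sample size as a purpose of the pilot.

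**What to change.** Delete the ICC gate in Preliminary Efficacy and in Secondary Efficacy and Implementation Outcomes, and make the Abstract agree. In its place:

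- For every two-arm outcome with several records per provider, always account for provider. Use either a random provider intercept with arm in the model, or GEE or cluster-robust standard errors, with a small-sample correction (for example t on about 44 − 2 = 42 df). Name the choice now.
- For scales collected only in the intervention arm, give provider-clustered intervals without an arm term.
- Report the ICC from a model that includes arm, with its confidence interval, as a descriptive result.

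The cost is about two sentences of text and slightly wider intervals for some outcomes. Where provider variance is estimated as zero, the mixed model's point estimates match ordinary regression. The Results section says that analyses are already under way, so the change should be dated and, if still possible, made before any comparison by arm is seen.
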